# Effect of *Daesiho-tang* on obesity with non-alcoholic fatty liver disease: a study protocol for a randomised, double-blind, placebo-controlled pilot trial

**DOI:** 10.1186/s13063-020-4068-y

**Published:** 2020-01-31

**Keywords:** Obesity, Non-alcoholic fatty liver disease, Herbal medicine, *Daesiho-tang*, *Dai-saiko-to*, *Dachaihu-tang*

## Abstract

**Background:**

The high prevalence of obesity and non-alcoholic fatty acid disease has become an important public health problem. *Daesiho-tang* (DST) is an herbal medicine widely used to treat obesity, metabolic syndrome and liver diseases. This pilot study will assess the feasibility of using DST in obese patients with a non-alcoholic fatty liver disease (NAFLD) prior to undertaking a full-scale clinical trial.

**Methods/design:**

This is a study protocol for a randomised, double-blind, parallel-group, stratified, placebo-controlled pilot trial. We will recruit a total of 60 participants with NAFLD who have a body mass index ≥ 25 kg/m^2^. They will take either DST or placebo (3 g, three times daily) for 12 weeks with a 4-week follow-up period. The effects of DST will be evaluated by the mean change in body weight as the primary measurement and other secondary parameters (body composition, anthropometric measurements, blood tests, hepatic fat quantification through transient elastography and a physical symptoms questionnaire). Faecal samples will be collected before and after the intervention for a gut microbial analysis.

**Discussion:**

In anticipation of conducting further large-scale trials, in this study we will explore the effect of DST on weight loss and obesity-related markers, along with NAFLD-related clinical parameters, in obese patients with NAFLD. Furthermore, it will provide insight into the DST pharmacological mechanism of action through a gut microbiome analysis.

**Trial registration:**

Korean Clinical Trial Registry, KCT0003554. Registered on 25 February 2019.

## Introduction

Approximately 39% of the world’s population was overweight or obese in 2015, and this figure will reach about 58% in 2030 [1, 2]. Obesity itself is considered a serious disease because it increases the risk of developing multiple diseases, such as diabetes mellitus, cardiovascular diseases, osteoarthritis and several cancers [3, 4]. Obesity is also the main cause of non-alcoholic fatty liver disease (NAFLD). NAFLD has the characteristic of hepatic fat accumulation in patients who do not use alcohol and may lead to insulin resistance, coronary heart disease, diabetes and serious liver diseases [5–7]. Authors of a retrospective cohort study reported that people with fatty liver have a three times increased risk of de novo metabolic syndrome [8]. Therefore, drugs for obesity and NAFLD are needed, but no definitive treatment exists. In general, NAFLD treatment is managed according to obesity, type 2 diabetes mellitus and hyperlipidaemia [9].

*Daesiho-tang* (DST; *Daichaihu-tang*, 大柴胡湯 in Chinese) is an herbal medicine widely used to treat obesity, metabolic syndrome and liver diseases in East Asian countries. DST consists of eight medical herbs, and the main active components are paeoniflorin, naringin, baicalin, baicalein, sennoside A, rhein, saikosaponin A and emodon [10]. Many animal studies have confirmed the anti-obesity, anti-diabetic and anti-hypertensive effects of DST [11–14]. Hussain et al. reported that DST ameliorates body weight gain in mice fed a high-fat diet by regulating leptin and adiponectin gene expression in adipose tissue [11]. Authors of in vivo and in vitro studies have reported that DST improves lipid metabolism by lowering hepatic triglyceride biosynthesis and by increasing low-density lipoprotein receptor gene expression in hepatocytes [15, 16]. However, no clinical data for DST are available regarding its use for obesity or NAFLD.

This pilot clinical trial is designed to verify the feasibility of DST for later large-scale clinical trials. This study will explore the effect of DST for modulating weight and correcting NAFLD-related parameters and will generate information on a suitable design to conduct further large-scale trials. Additionally, changes in the gut microbial community will be analysed using a sequence-based metagenomic analysis to provide insight into the pharmacological mechanisms of DST in gut microbiota.

## Methods/design

### Study aim and objectives

The aim of this trial is to pilot study procedures and assess feasibility prior to undertaking a full-scale clinical trial on DST to control body weight in obese patients with NAFLD. The primary objective is to assess the feasibility of DST in weight loss compared with placebo in obese patients with NAFLD. The secondary objective is to determine the efficacy of DST in metabolic disease-related parameters, such as waist and hip circumference, body composition, blood analysis, transient elastography analysis, NAFLD-related physical discomfort and obesity-related quality of life. As an exploratory outcome, changes in the gut microbial community will be analysed to evaluate the effect of DST on the gut microbiota.

### Study design

This study is a randomised, double-blind, parallel-group, stratified (by gender), placebo-controlled pilot clinical trial. It will be conducted at Dunsan Korean Medicine Hospital, Daejeon University, Daejeon, Republic of Korea. A total of 60 participants will be recruited by local advertisements and the hospital bulletin board. All participants will be asked to sign the latest version of the informed consent form approved by the local institutional review board (IRB). When subjects voluntarily decide to participate, they will undergo screening, and specialists in Korean medicine will confirm their eligibility based on the inclusion and exclusion criteria. If a subject has been qualified to participate, they will be invited for a baseline assessment within 2 weeks. At the second visit, subjects will be randomly allocated to either the DST group or the placebo group in a 1:1 allocation ratio. Participants will take either DST or the placebo drug for 12 weeks. Participants will visit once monthly for evaluation while taking the test drugs. A follow-up assessment will be performed 4 weeks after the final drug administration. The study flowchart is presented in Fig. 1, and a detailed schedule of enrolment, interventions and assessments is given in Fig. 2.

**Fig. 1 Fig1:**
[figure not shown]
Study flowchart

**Fig. 2 Fig2:**
[figure not shown]
Schedule of enrolment, interventions and assessments

### Participants

#### Inclusion criteria

Adults over 19 years to under 65 years of ageObese subjects with body mass index ≥ 25 kg/m^2^Subjects with non-alcoholic fatty liver findings on transient elastography: controlled attenuation parameter (CAP) score > 268 dB/mThose who have voluntarily signed a written consent form approved by the IRB after sufficient explanation of this study

#### Exclusion criteria

Subjects who have had weight changes > 10% of their previous weight within the last 6 monthsSubjects who are already on a diet or undertaking heavy exercise for weight control purposesSubjects who have undergone surgical procedures for weight controlPatients with endocrine disease that may affect body weight, such as hypothyroidism, Cushing’s syndrome, or those with thyroid-stimulating hormone concentration < 0.1 uIU/ml or > 10.0 uIU/mlPatients with evidence of chronic hepatitis, such as hepatitis B, hepatitis C (HCV), autoimmune hepatitis and metabolic hepatitis (hepatitis B surface antigen [HbsAg] or HCV antibody-positive in screening tests)Subjects with alcohol intake > 210 g per week for men and > 140 g for women during the last yearLiver stiffness measurement (LSM) of 12.5 kPa or higher by transient elastographySubjects who have received liver transplantsSubjects who use insulin injections to control blood glucose concentrationSubjects taking thiazolidinediones and high-dose vitamin E that may affect NAFLDThose who have taken drugs that can be used to treat obesity, antidepressants, contraceptives, oral steroids, amphetamines, phenodiazines, cyproheptadines, female hormones or thyroid hormones within 3 months of screening (short-term use of prednisone or equivalent corticosteroids < 10 mg/day within 7 days, which may not affect body weight, will be allowed [17])Those whose aspartate transaminase or alanine transaminase exceeds five times the normal upper limit (200 IU/L)Kidney dialysis patients or those with creatinine concentration more than twice the normal upper limitThose who are in seriously unstable medical condition, such as cardiovascular disease, respiratory disease, gastrointestinal disease, hepatobiliary disease, metabolic disease, endocrine disease, renal disease or problems in the urinary reproductive system and nervous systemThose who have had a diagnosis or have been treated for malignant tumours within the last 5 yearsWomen who are pregnant or lactating, or subjects who do not agree to use effective methods of contraception during the clinical trial (Oral contraceptives are not allowed during the clinical trial.)Subjects with genetic problems, such as galactose intolerance, Lapp lactase deficiency, or glucose-galactose malabsorptionSubjects with a history of alcohol abuse or drug abuse within the past yearSubjects who have taken other clinical trial drugs within 3 monthsSubjects who are thought to be inappropriate for this study

### Sample size

This study is a pilot clinical trial to explore the feasibility of DST in obese subjects with NAFLD. No clinical trial has evaluated the efficacy of DST for weight loss and/or NAFLD. Therefore, we calculated sample size based on an opinion from an expert in medical statistics and clinical trials similar to this study that had used herbal supplements for weight loss [18, 19]. According to the previous studies, we assumed the mean and standard deviation of body weight would be 2.2 kg and 2.7, respectively. Thus, the sample size was 30 subjects in each group with a significance level of 5%, power of 80% and drop-out rate of 20%. A total of 60 subjects will be recruited and divided into two groups of 30 subjects each.

### Randomisation and allocation concealment

Subjects will be randomly allocated to either the DST or placebo group in a 1:1 allocation ratio. Among the various factors affecting the development of obesity and NAFLD, gender differences are the most important factor [20–22]. Because gender differences in NAFLD may have a different impact on the progression of complications, such as non-alcoholic steatohepatitis (NASH), liver fibrosis and hepatocellular carcinoma, subjects were stratified according to gender [23]. The gender distribution for each group will be controlled by an independent statistician using the stratified block randomisation method. The statistician will use SAS version 9.4 software (SAS Institute, Cary, NC, USA) to generate a random allocation list and will send the list to the pharmaceutical company for packing. The allocation for each subject will be sealed in an opaque envelope and will not be disclosed until the clinical trial is completely over, unless serious adverse events (SAEs) happen.

### Blinding

A statistician who is not involved in the clinical trial will send the randomisation codes to the pharmaceutical company for packing to maintain blindedness of the assessors and the subjects. The placebo drug was manufactured in a form similar to DST by the same pharmaceutical company. It was confirmed in advance that the taste and flavour were similar (Additional file 1). According to the randomisation sequence, drugs will be packed in the same form and will be delivered to the hospital. During the trial period, the pharmacist will supply the drug sequentially according to the randomisation code. To evaluate whether the blinding is successful, a quick questionnaire will be completed at the end of the study. All subjects were asked the same questions at the end of the intervention: ‘Do you think the test drug you took is a real drug or a placebo? And why do you think so’?

### Intervention

Participants in both groups will take DST or the placebo drugs three times daily (3 g/packet at a time) for 12 weeks. The drugs will be distributed on a monthly basis. Both the DST and placebo drugs will be manufactured by Hanpoong Pharmaceutical (Wanju, Republic of Korea) according to good manufacturing practice guidelines. Both drugs will be prepared in the form of dark brown granules. The constituents of DST are shown in Table 1. The DST granules contain DST soft extract, lactose hydrate and corn starch. The placebo drug contains lactose hydrate, corn starch, caramel colour and ginseng-flavoured powder. Ginseng-flavoured powder is a food ingredient without any medicinal effect that only gives off the flavour of ginseng. To assess adherence to the intervention, the subjects will be told to bring the empty packet of the ingested test drug and the leftover. Subjects who have < 70% drug compliance at the end of the study will be dropped out. The research team will periodically contact subjects by phone or text message to improve compliance and check for safety.

**Table 1 Tab1:** Constituents contained in a single dose of *Daesiho-tang* soft extract

Constituents	Botanical names	Content (g)
Paeoniae Radix (芍藥)	*Paeonia lactiflora* Pallas	1^a^
Scutellariae Radix (黃芩)	*Scutellaria baicalensis* Georgi	1^b^
Zingiberis Rhizoma Recens (生薑)	*Zingiber officinale* Roscoe	1.67
Ponciri Fructus Immaturus (枳實)	*Poncirus trifoliata* Rafinesque	0.67
Bupleuri Radix (柴胡)	*Bupleurum falcatum* Linné	2
Pinelliae Tuber (半夏)	*Pinellia ternata* Breitenbach	1.33
Rhei Radix et Rhizoma (大黃)	*Rheum officinale* Baillon	0.67
Zizyphi Fructus (大棗)	*Ziziphus jujuba* Miller var. inermis Rehder	1

^a^20 mg as paeoniflorin

^b^100 mg as baicalin

### Permission for use of concomitant drugs

Prohibited drugs include agents that can affect the primary outcome of body weight, such as anti-obesity medications, antidepressants, amphetamines, oral contraceptives, hormone drugs, oral steroids, cyproheptadine and phenothiazine. Agents that can affect NAFLD, such as insulin, thiazolidinedione and high-dose vitamin E (> 800 IU per day) are also prohibited. Lipid-lowering agents, anti-diabetic medication and hepatoprotective agents are not included as prohibited drugs, but subjects should not take them as much as possible unless they were taking it from the screening visit. Drugs that can cause significant changes in the gut microbial community, such as antibiotics and lactic acid bacteria, are not prohibited, but subjects should avoid them as much as possible to minimise the effect on intestinal microorganisms.

### Lifestyle guidelines

The subjects will be told to maintain their usual exercise routine and not to change the amount of exercise or kind of exercise they engage in. The Korean version of the International Physical Activity Questionnaire Short Form will be administered to evaluate physical activity status [24]. Daily intake of a low-calorie 20–25-kcal/kg diet will be recommended to increase the weight loss effect. Food intake status will be investigated using 3-day dietary recall before and after the drug intervention. Can-Pro version 5.0 (a computer-aided nutritional analysis program for professionals; Korean Nutrition Society, Seoul, Korea) will be used for the dietary data analysis. Can-Pro is commonly used in Korea to assess nutrient intake because it has a database that reflects the Korean diet.

### Assessments

#### Anthropometric measurements

Body weight will be assessed at every monthly visit, including the screening visit. Waist circumference and hip circumference will be measured according to the World Health Organisation’s instructions at every monthly visit [25]. Anthropometric measurements will be performed by the same person to minimise errors.

#### Body composition

Body composition, such as fat percentage, fat mass and lean body mass, will be measured at every monthly visit using a body composition analyser (InBody 770; Biospace Ltd., Seoul, Korea). The body mass index will be calculated as weight in kilograms divided by height in meters squared.

#### Non-alcoholic fatty liver assessment

Transient elastography, also called a Fibroscan analysis (Fibroscan 530 Compact; Echosens, Paris, France) will be completed by a trained operator after at least 2 h of fasting. The transient elastography analysis is a non-invasive test to assess liver steatosis and fibrosis. Recent studies have shown that the CAP value is a reliable marker to quantify hepatic steatosis [26–28]. LSM values will also be obtained.

#### NAFLD-related symptoms

Physical symptoms related to NAFLD will be assessed using a visual analogue scale (VAS). The VAS is one of the most widely used measures to evaluate subjective symptoms [29–31]. Participants will be asked to mark their degree of fatigue and abdominal discomfort on a 100-mm horizontal line, where 0 indicates ‘no fatigue/discomfort’ and 100 indicates ‘the worst fatigue/discomfort’. Assessors will record the length between the points marked by the subject.

#### Korean version of Obesity-related Quality of Life (KOQOL) questionnaire

The KOQOL questionnaire was developed to evaluate quality of life in obese patients by reflecting the cultural and linguistic expression of Koreans [32]. The reliability and validity of the KOQOL has been verified (Cronbach’s α, 0.6–0.8) [32]. The KOQOL consists of 15 questions and 6 domains: psychological health, physical health, work-related quality of life, routine life, sex life and diet distress (Additional file 2). The total possible score is 60, and the higher the score, the lower the quality of life.

#### Obesity pattern identification questionnaire

The obesity pattern identification questionnaire was developed by the Korean Institute of Oriental Medicine to categorise obese patients into different constitutions, which is the fundamental basis of Korean traditional medicine [33, 34]. Obese subjects can be classified into six patterns: spleen deficiency, yang deficiency, food accumulation, liver depression, phlegm fluid and blood stasis. The questionnaire will be completed at the screening visit (Additional file 3). The obesity pattern of each subject can be used in a subgroup analysis to evaluate whether treatment effects differ according to the obesity pattern.

#### Blood testing

Blood testing will be done at the screening visit, after 12 weeks of drug intervention and at the follow-up visit (week 16). The blood tests will include aspartate aminotransferase, alanine aminotransferase, alkaline phosphatase, total bilirubin, direct bilirubin, γ-glutamyl transpeptidase, blood urea nitrogen, creatinine, protein, albumin, uric acid, white blood cells, red blood cells, erythrocyte sedimentation rate, haemoglobin, haematocrit and platelets. It will also include glucose, insulin, total cholesterol, low-density lipoprotein cholesterol, high-density lipoprotein cholesterol and high-sensitivity C-reactive protein. Haemoglobin A1c will be examined at the screening and after 12 weeks of drug intervention. Thyroid-stimulating hormone, HbsAg, anti-HCV and urine human chorionic gonadotropin (only women of childbearing age) will be evaluated at the screening visit to determine eligibility.

#### Safety assessment

Blood pressure, heart rate and body temperature will be measured at every visit using an automated device. Participants will be asked if they have any physical discomfort. The frequency of adverse events (AEs) will be presented for the safety assessment. Any AEs will be recorded on the electronic case report form (eCRF) after assessing severity and causality. If an SAE occurs, it will be reported to the IRB as soon as possible. The study physicians will follow up with all participants reporting AEs and will perform medical evaluations to determine the cause of the AE and its possible relationship to the interventions. Additional blood tests may be performed at any time if necessary, and during the study, subjects who meet the exclusion criteria will be dropped out of the study for their safety.

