### Outcome measures

Because this is a pilot trial, the recruitment rate and completion rate will be calculated to determine feasibility of the study design. The primary outcome of this study will be the mean change in body weight from baseline to the end of the 12-week intervention. Secondary outcomes will include body composition and anthropometric measurements. A transient elastography and physical symptoms questionnaire will be completed at every monthly visit.

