### Statistical analysis

The statistical analysis will be conducted by an independent statistician using SAS version 9.4 software. The significance level will be set to 5% in a two-tailed test. The multiple imputation method will be adopted for missing data. The intention-to-treat (ITT) principle will be applied for the primary analysis. The ITT principle will include subjects who meet the full analysis set criteria, including subjects who had the primary outcome assessed once or more except for the baseline measures and who took the test drug at least once. The per-protocol set will be analysed in a supplementary analysis, which will only include subjects who have completed the study as the supplementary analysis.

The independent *t* test or Wilcoxon rank-sum test will be used for continuous variables, and the chi-square test or Fisher’s exact test will be used for categorical variables. Analysis of covariance will be performed for the primary outcome and the continuous data of the secondary outcomes. The model will include baseline values and gender as covariates and treatment as a fixed effect. Student’s *t* test or Wilcoxon’s signed-rank test will be used to compare data before and after the treatment within each group. Categorical data will be analysed using the chi-square test or Fisher’s exact test. Additionally, repeated measures analysis of variance will be used to compare differences in trends per visit.

The incidence of SAEs and AEs related to the treatment will be analysed. The percentage of subjects who experience one or more side effects during the study will be analysed and presented using a descriptive analysis for each group.

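### The on-study exclusion rule ends study participation, so week-12 weight is likely to be missing for reasons that can be related to treatment, in a primary analysis described as intention-to-treat

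*Protocol article*

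**What the plan says.** All references are to the protocol article.

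- Safety assessment: during the study, "subjects who meet the exclusion criteria will be dropped out of the study for their safety". Just before this, the same section keeps medical follow-up of adverse events: "The study physicians will follow up with all participants reporting AEs and will perform medical evaluations to determine the cause of the AE".
- Outcome measures: "The primary outcome of this study will be the mean change in body weight from baseline to the end of the 12-week intervention".
- Statistical analysis: "The intention-to-treat (ITT) principle will be applied for the primary analysis". The set that carries this label is then limited, "including subjects who had the primary outcome assessed once or more except for the baseline measures and who took the test drug at least once". For gaps: "The multiple imputation method will be adopted for missing data". No imputation model, missingness assumption or donor arm is given.
- Assessments: weight is taken at each monthly visit. Blood tests are due at screening, week 12 and week 16.
- Exclusion criteria: the list mixes items that can arise from treatment (AST or ALT above five times the upper limit, creatinine above twice the limit, a seriously unstable medical condition) with items that are not safety events (being on a diet, taking antidepressants) and one that is close to the outcome itself (a weight change above 10% within six months).

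**The concern.** The rule gives safety as its reason and removal from the study as its consequence. The article nowhere separates taking the test drug from being assessed. Followed as written, a subject who meets one of these criteria at week 4 or week 8 has no week-12 weight.

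An intention-to-treat analysis compares the groups as randomised and needs the outcome whatever happened to treatment. Here the protocol itself stops the outcome from being collected, in subjects whose removal may have been caused by the treatment. Two consequences follow. Subjects with some post-baseline weight enter the analysis with an imputed week-12 value. Subjects removed before any post-baseline weight are not imputed; they are left out.

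At stake is whether the estimate describes the effect of being assigned DST or something closer to the effect had nobody stopped. This is a pilot meant to inform a larger trial, so its estimate may be carried forward. Removals required by the rule also count against the completion rate, which is one of the feasibility measures.

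**Working it through.** **1. The plan's own figure.** The Sample size section gives 2.2 kg, SD 2.7, 5% significance, 80% power, 20% drop-out and 30 per group; the Statistical analysis section makes the test two-sided. The article does not say that 2.2 kg is a between-group difference, so I read it that way as an assumption.

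n per arm = 2 × (1.96 + 0.84)² × (2.7/2.2)² ≈ 23.6, rounded up to 24. Then 24/0.8 = 30. The stated figure reproduces under this reading. The t-based version gives 24.6, so 25 per arm and 32 after inflation.

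**2. The statements side by side.**

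| Statement | What it needs or does |
|---|---|
| Outcome: weight change to week 12 | A weight at week 12 for each subject |
| Intention-to-treat primary analysis | That weight whatever the treatment status |
| On-study exclusion rule | Ends participation, with no later weighing described |
| Analysis set | Leaves out anyone with no post-baseline weight |
| Multiple imputation | Fills the remaining gaps by an unstated model |

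The first two cannot be met for a subject to whom the third applies before week 12. If everyone removed under the rule lacks a week-12 weight, no off-drug week-12 data from these subjects exist to inform any imputation model.

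**3. Size of the possible bias.** Let d be the share of the DST arm removed and r the share of the effect that persists after stopping. Both are my assumptions; the article gives only the overall 20% drop-out.

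Effect of assignment = 2.2 × (1 − d + d·r). Within-arm missing-at-random imputation that ignores the subject's earlier weights centres on 2.2. The overstatement is therefore 2.2 × d × (1 − r).

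| d | Effect, r = 0 | Overstatement, r = 0 | Overstatement, r = 0.5 | Overstatement, r = 1 |
|---|---|---|---|---|
| 5% | 2.09 kg | 0.11 kg (5.3%) | 0.055 kg | 0 |
| 10% | 1.98 kg | 0.22 kg (11.1%) | 0.11 kg | 0 |
| 20% | 1.76 kg | 0.44 kg (25%) | 0.22 kg | 0 |

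Percentages are relative to the effect of assignment, for example 0.44/1.76 = 25%.

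**4. Check by simulation.** Settings: 30 per arm, 20 imputations, 1,500 runs, the same share removed at random in each arm, and no interim weights in the model.

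| d | r | All weighed at week 12 | Imputed within arm |
|---|---|---|---|
| 20% | 0 | 1.76 kg | 2.20 kg |
| 20% | 0.5 | 1.97 kg | 2.19 kg |
| 10% | 0 | 2.00 kg | 2.24 kg |
| 10% | 0.5 | 2.06 kg | 2.17 kg |

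These agree with the formula apart from simulation error.

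**5. Power if everyone is weighed.** With all 30 per arm measured, power (normal approximation) is 0.88 at 2.20 kg, 0.81 at 1.98 kg and 0.71 at 1.76 kg.

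**The case against.** The strongest reply is that this is a condensed article. The full protocol (version 1.4) and any analysis plan are not shown, and retention procedures and imputation models commonly sit there. This stands for the imputation model. It does not stand for the rule: removal from the study is stated outright, not left out. An analysis plan also cannot recover weights that were never taken.

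A reader might infer several stronger things, which the article does not support:

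- That multiple imputation will credit removed subjects with the result of those who stayed on drug. Only the method is named. Imputation based on the placebo arm would not do this, and a usual model would also draw on the subject's own monthly weights.
- That the bias favours DST. No adverse-event or discontinuation rates by arm are given. Read literally on study, the criterion on weight change above 10% could remove strong responders, which pushes the other way.
- That safety follow-up is lost. Physicians follow up everyone who reports an adverse event. What is at risk is the scheduled week-12 and week-16 assessments. The Study design section places the follow-up visit four weeks after the last dose, but for an early stopper that falls at week 12 only if the last dose was at week 8.
- That the rule covers every subject stopped for safety. It covers those who meet an exclusion criterion, and some criteria are not safety matters.
- That the compliance rule does the same harm: "Subjects who have < 70% drug compliance at the end of the study will be dropped out". It is applied at the end of the study, when week-12 weight may already exist, so it is a separate question.

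It is also fair to say that 20% removal under this one rule has no basis in the article, and that a pilot's efficacy estimate carries less weight than a confirmatory one.

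**Conclusion.** The point holds as a conflict between the on-study exclusion rule and the intention-to-treat analysis of week-12 weight. It should be repaired, because the data loss comes from the protocol and can be tied to treatment.

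The size is modest and conditional. Taking 2.2 kg as the between-group effect and within-arm missing-at-random imputation, the overstatement runs from 0 kg to at most 0.11, 0.22 or 0.44 kg for removal of 5%, 10% or 20% of the DST arm. The upper figures assume that no effect persists after stopping and that interim weights are not used; the last also assigns the whole all-cause planning drop-out to this rule. The sign would be uncertain if the weight-change criterion were applied literally. Confidence is medium, since the full protocol may already provide for continued assessment.

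**What to change.** Reconcile the Safety assessment and Statistical analysis sections without changing when or whether treatment is stopped, which is a clinical matter and not judged here.

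- State that subjects removed under the on-study exclusion rule remain in the scheduled outcome and safety visits to weeks 12 and 16 unless they withdraw consent.
- State that their measured week-12 weight is used in the primary analysis whatever their treatment status. Those removed before their first post-baseline weight would then normally have one and stay in the analysis set.
- Optionally, add a sensitivity analysis that imputes from the placebo arm where week-12 weight is still missing.

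The cost is a short amendment, a few visits by subjects off drug (the visits are already scheduled) and, if chosen, one extra analysis. The downside is a possibly smaller effect estimate. Recruitment has already begun, so the change helps only subjects whose scheduled visits are still to come.
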